## STUDY SUMMARY IN LOCAL LANGUAGE

Die Haut- und Nasendekolonisation von Patienten vor allgemeiner elektiver Chirurgie ist in mehreren Guidelines empfohlen. Die tägliche prä-operative Dekolonisation mit topischen Mitteln und Salben zielt auf die Reduktion von postoperativen Wundinfekten. Die Literatur unterstützt diese Maßnahme vor allem bei Patienten mit nachgewiesener Hautkolonisation mit *Staphylococcus aureus* und bei chirurgischen Eingriffen mit hohem Risiko von postoperativen Infekten. Der optimale Ablauf ist unbekannt. In der Literatur dauert sie zwischen drei bis sieben Tagen vor elektiver Chirurgie und betrifft meistens die alleinige Nasendekolonisation; und seltener die Ganzkörperdekolonisation mit einschliesslich der Nasensalbe.

Auf der anderen Seite ist diese generelle Dekolonisation organisational sehr aufwändig und auch nicht immer erfolgreich in allen Studien, welche alle Patienten zusammen untersucht hatten. In der orthopädischen Chirurgie, in der die Infektionsrate traditionell niedriger ist als bei anderen chirurgischen Disziplinen, könnten eventuell nur ausgesuchte Patienten von der Dekolonisation profitieren. Zugleich sind orthopädische Operationen meistens mit Implantaten vergesellschaftet, dessen Infektionen mehrheitlich durch (Koagulase-negative) Hautkeime verursacht sind, welche wiederum (im Gegensatz zu *S. aureus*) nicht durch die perioperative Standard-Prophylaxe abgedeckt wären. Letztendlich spielt die Patientencompliance eine Rolle. Das Vorhandensein von Dekolonisations-Set wäre eine substantielle Vereinfachung der Prozedur, anstatt den Patienten ein Rezept abzugeben (welches diese verwenden oder nicht).

Gezielte prospektive-randomisierte Studien unter orthopädischen Patienten mit erhöhtem Infektrisiko, welche das Resultat der Dekolonisation von allen potentiellen (Prophylaxe-resistenten) Hautkeimen untersuchen sowie die Patienten-Compliance erfragen, existieren in der Literatur nur ansatzweise.

Wir möchten solch eine Studie durchführen mit Hilfe eines Dekolonisations-Sets. Diese Studie ist mit Kosten verbunden, welche freundlicherweise von der Firma Schülke mit einer Spende über 55'000 CHF (20% Lohn einer Study Nurse während 2 Jahren) sowie einer Spende von 550 Dekolonisations-Sets unterstützt werden. Der Sponsor und der Principal Investigator sind vom Balgrist. Die Spende hat keinen Einfluss auf Durchführung und Publikation der Studie.

## ABBREVIATIONS

|         |                                                                     |
|---------|---------------------------------------------------------------------|
| AE      | Adverse Event                                                       |
| ASA     | American Society of Anesthesiologists                               |
| ASR     | Annual Safety Report                                                |
| CA      | Competent authority                                                 |
| CEC     | Competent Ethics Committee                                          |
| CRP     | Serum C-reactive protein                                            |
| eCRF    | Electronic case report forms                                        |
| EOT     | End of treatment                                                    |
| GCP     | Good Clinical Practice                                              |
| ICH-GCP | International Conference on Harmonization of Good Clinical Practice |
| IMM     | Institut für Medizinische Mikrobiologie                             |
| NRS     | Nutritional Risk Screening                                          |
| REDCap  | Research Electronic Data Capture                                    |
| SAE     | Serious Adverse Events                                              |
| SNCTP   | Swiss National Clinical Trials Portal                               |
| SSI     | Surgical Site Infection                                             |
| SOP     | Standard Operation Procedure                                        |
| SUSARs  | Suspected Unexpected Serious Adverse Reactions                      |
| UCAR    | Unit for Clinical and Applied Research                              |
| VAC     | vacuum-assisted negative pressure                                   |
| ZLZ     | Zentrallabor Zürich                                                 |

## STUDY SCHEDULE

### Randomized-controlled trial

| Study Periods                            | Screening/
Baseline* | Visit 1*
Enrol-
ment | Visit 2*
End-of-
Treatment                 | Visit 3
Test-of-Cure  | Follow-up for surger-
ies with implants |
|------------------------------------------|-------------------------|----------------------------|--------------------------------------------------|--------------------------|--------------------------------------------|
| Time                              | Day -30 to 0            | Enrolment                  | Surgery day or 1-
2 days after the
surgery | 6 weeks
(+/- 14 days) | 1 year
(+/- 2 months)                   |
| In-/ Exclusion criteria                  | X                       | X                          |                                                  |                          |                                            |
| Informed consent                         | X                       | X                          |                                                  |                          |                                            |
| Demographics / history                   | X                       | X                          |                                                  |                          |                                            |
|                                          |                         |                            |                                                  |                          |                                            |
| Concomitant medication                   |                         | X                          | X                                                | X                        | X                                          |
| Randomization                            | X                       | X                          |                                                  |                          |                                            |
| Handing out of the
decolonization set |                         | X                          | X                                                |                          |                                            |
| Questionnaire                            |                         |                            | X                                                | X                        |                                            |
| Compliance                               |                         |                            | X                                                | X                        | X                                          |
| Adverse Events                           |                         | X                          | X                                                | X                        | X                                          |
| Study End                                |                         |                            |                                                  | X                        | X                                          |

We assess:

Patient's characteristics (age, sex, body mass index, renal insufficiency, cirrhosis, other immune-suppressions, diabetes, pregnancy), indication of surgery, presence of osteosynthesis, all postoperative complications, surgical site infections and pathogens, all adverse events during hospitalization, length of hospital stay, duration of an eventual VAC (vacuum-assisted closure) / PICO use, and the patient's opinion on the use of the decolonization set (patient questionnaire) immediately after surgery.

The previously validated questionnaire will be in German language with five open questions: Practical difficulties of decolonization, the completeness of scheduled decolonization actions, all adverse events during decolonization and surgery, and two questions regarding the comprehension of the science (indication for decolonization, potential benefit expected in the individual case).

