The duration of pre-surgical decolonization is planned to be five days. However, when this pre-surgical time period is too short, the decolonization may also start at least 3 days before surgery and be continued up to 2 days post-surgery. During the post-surgery application, the patient will be washed with water and octenisan® by their treating nurses. The patient will also return the empty/used set and answer to a short questionnaire during their hospital stay. The study team will recuperate the questionnaire during hospitalization. We renounce on routine microbiological assessments of skin colonization, but the hospital's infection control can demand it for other reasons regarding infection control. Hence, skin colonization data will only be available for some selected patients that are screened for body carriage of antibiotic-resistant pathogens, according to the infection control recommendations in Switzerland.

There will be a Monitoring at study start, the interim analysis and at the end.

The primary study outcomes are unplanned revision surgery for SSI and wound problems at 42 days for all surgeries; or 1 year in case of an implant-related surgery. Secondary objectives are other unplanned revision surgeries for non-SSI reasons, all adverse events, as well as patient's subjective impression of the decolonization.

The treatment period includes the following daily study visits:

- Visit 1 - Enrollment (Day 1)
- End-of-Treatment (EOT) -Visit is the Day of Surgery or Day 1-2 after surgery
- Test-of-Cure-Visit (TOC) (clinical surgical control) - Day 42 (+/- 14 days)
- Further follow-up (eventually by phone call) for implant-related surgery - 1 year (+/- 2 months)

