#### 8.1.1 Intervention treatment

The duration of pre-surgical decolonization is planned to be five days. However, when this pre-surgical time period is too short, the decolonization may also start at least 3 days before surgery and may be continued up to 2 days post-surgery. In case of post-surgery application, the patient will be washed with water and octenisan® wash lotion by their treating nurses. The patient will also return the empty/used set and answer to a short questionnaire during their hospital stay. The study team will recuperate the questionnaire during hospitalization.

During decolonization, patients are asked to change the bed linen and underwear every day and not to share towels, clothes and other textiles with their family or pets. They may use their habitual perfumes, but must not use other antiseptic agents, body lotions or moisturizer during the decolonization period.

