### 8.3 Compliance with study intervention

We assess the auto-declared compliance of the patients in the intervention (decolonization) arm via questionnaires and by recuperating the empty packages of the decolonization sets.

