#### 8.7 Accountability of the investigational product

We recuperate the packages of the used decolonization sets from the patients during hospitalization and/or shortly after surgery and this process will be documented (e.g. accountability log). This log should also serve to record any damages of the set.

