#### 11.3.2 Final analyses

The intent-to-treat (ITT) population will consist of all randomized patients. Patients will be analysed according to treatment group assignment. Patient disposition and baseline characteristics will be based on the ITT population.

The per-protocol (PP) population will consist of all randomized patients who complete the study (or who are otherwise defined as a treatment failure) according to the clinical investigation plan and who have not deviated significantly from the protocol. All efficacy analyses will be repeated using the PP population. Any analysis involving microbiological assessments will exclude patients without an assigned baseline pathogen.

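### The schedule table marks the questionnaire at 6 weeks and compliance at 6 weeks and 1 year, against the in-hospital timing in the text, so compliance could be recorded after the outcome is known

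*Protocol*

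**What the plan says.** The Study Schedule table has a row labelled "Questionnaire", marked at Visit 2 (surgery day or 1-2 days after) and again at Visit 3 (6 weeks). The row below it, for compliance, is marked at Visit 2, at Visit 3 and at the 1-year follow-up for implant surgery.

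The text gives an earlier and single timing:

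- Directly under the table, the item collected is "the patient's opinion on the use of the decolonization set (patient questionnaire) immediately after surgery".
- Synopsis, Study Conduct: "The study team will recuperate the questionnaire during hospitalization".
- Section 8.1.1: "The patient will also return the empty/used set and answer to a short questionnaire during their hospital stay".
- Section 8.7: "We recuperate the packages of the used decolonization sets from the patients during hospitalization and/or shortly after surgery".

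Section 8.3 is the only place that says how compliance is measured: "We assess the auto-declared compliance of the patients in the intervention (decolonization) arm via questionnaires", together with the returned empty packages. The questionnaire carries the compliance item, since one of its topics is "the completeness of scheduled decolonization actions". Section 8.1.2 gives control patients neither decolonization nor questionnaire.

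On exclusions, section 11.3.2 keeps in the per-protocol set those "who have not deviated significantly from the protocol". Section 11.4 turns missing data on the decolonization into a dropout, and removes major deviations from both the per-protocol and the intention-to-treat populations.

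**The concern.** Under section 8.1.1 the regimen ends at the latest 2 days after surgery. By 6 weeks or 1 year, all that can still be collected about it is a retrospective account. Those two visits are also when the primary outcome is assessed (section 5), and patients know their arm (section 6.2.2). A patient with a failed wound, or the staff asking, may describe the decolonization differently from a patient whose wound healed.

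If such an answer then decided who deviated from the protocol, membership of an analysis set would depend partly on the outcome. It would do so in one arm only, because controls have no compliance measure. Section 11.4 as written would let this reach the intention-to-treat comparison as well as the per-protocol one. An opinion on the set given at 6 weeks could likewise reflect how the wound did.

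**Working it through.** **1. Table against text**

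| Item | Schedule table | Text |
|---|---|---|
| Questionnaire | Visit 2 and 6 weeks | Once, in hospital or immediately after surgery (Study Conduct, text under the table, 8.1.1) |
| Compliance | Visit 2, 6 weeks and 1 year | Measured by questionnaire and returned packages (8.3), both collected in hospital or shortly after surgery (8.1.1, 8.7) |
| Visit 3 procedures | Both items marked | Neither item listed (9.2.3) |
| 1-year procedures | Compliance marked | Not listed (9.2.4) |

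The text therefore times both compliance instruments, and times them early. At 6 weeks the table adds a second questionnaire, hence a second compliance answer. At 1 year it marks compliance with no questionnaire, when the packages are already back. That mark has no described data source.

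**2. What is known at the late visits**

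For implant-free surgery the outcome is complete at 6 weeks. For implant surgery only early events are known then, and the full outcome is known at 1 year.

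**3. Route into the analysis**

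Sections 11.3.2 and 11.4 remove patients for deviation or for missing decolonization data. Neither says which compliance record counts, nor that the classification is made before the outcome is known. Neither says that incomplete decolonization is a significant or major deviation.

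**4. The plan's own figure**

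Inputs from sections 11.1 to 11.3 are 10% against 5%, two-sided 0.05, 80% power and 1:1 allocation. The pooled two-proportion formula gives 435 per arm. With the continuity correction it gives 474, the plan's figure, which the plan rounds up to 500. This is not in dispute.

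**5. Illustration of size**

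The documents give no exclusion rates, so all rates here are assumptions. Take no true effect, 500 per arm and 10% events, that is 50 events and 450 event-free patients in each arm. Let a share f0 of event-free patients and f1 of event patients be excluded in the decolonization arm only.

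Apparent risk = 50(1 - f1) / [50(1 - f1) + 450(1 - f0)], against 50/500 = 10% in control.

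| f0 | f1 | Calculation | Apparent risk | Difference from 10% |
|---|---|---|---|---|
| 5% | 5% | 47.5/(47.5 + 427.5) | 10.0% | 0 |
| 5% | 15% | 42.5/(42.5 + 427.5) | 9.04% | 0.96 points |
| 5% | 20% | 40/(40 + 427.5) | 8.56% | 1.44 points |
| 5% | 30% | 35/(35 + 427.5) | 7.57% | 2.43 points |
| 5% | 0% | 50/(50 + 427.5) | 10.47% | -0.47 points |

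Rows two to four correspond to 0.96/5 = 19%, 1.44/5 = 29% and 2.43/5 = 49% of the planned 5-point effect. The last row shows that the sign reverses if event patients are the less often excluded.

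A simulation of 400,000 trials with f0 = 10% (uncorrected pooled z-test, two-sided 0.05) gives these type I errors:

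- f1 = 10%: 5.0%
- f1 = 20%: 8.1%
- f1 = 30%: 19%
- f1 = 50%: 66%

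Exclusion that does not depend on outcome leaves both the risk and the error rate intact.

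**The case against.** The strongest reply is that these are stray marks. The same table also marks randomization at both screening and enrolment, and handing out of the set at End-of-Treatment. The visit lists do not carry out the late items. The compliance row might mean adherence to study visits, since section 7.4 speaks of non-compliance in that wider sense. Detailed per-protocol rules also commonly sit in a statistical analysis plan, which is not at hand.

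Much of this stands. It does not remove the contradiction, because staff who follow the table would collect late answers. Section 8.3 gives decolonization compliance as the only definition. When data are collected is set by this protocol, and a later analysis plan cannot make a late answer independent of the outcome, although it could decline to use it.

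A reader might go further and infer any of the following, none of which the documents support:

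- **Late answers will decide exclusions.** No section says so.
- **The table alone sets the compliance times.** Sections 8.1.1 and 8.7 time both instruments.
- **Every outcome is known at 6 weeks.** For implant surgery it is not.
- **The bias favours decolonization.** This is plausible, but patients could equally overstate their adherence.

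**Conclusion.** The concern holds as a contradiction between the schedule table and the text. Followed as written, the table permits compliance in one arm of an open trial to be recorded when the outcome is fully or partly known. The exclusion rules in sections 11.3.2 and 11.4 do not prevent such a record from being used.

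No bias is demonstrated. The apparent benefit of 1.0 to 2.4 points, and the inflated type I errors, are arithmetically right but rest wholly on assumed exclusion rates and an assumed direction. They show that the matter is not negligible if late answers were used, and nothing more.

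The removal of major deviations from the intention-to-treat set in section 11.4 is a fault in its own right. It matters here because it would carry the problem beyond the per-protocol analysis, and because it affects how the remedy must be worded.

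**What to change.** - **Schedule table:** delete the questionnaire mark at Visit 3 and the compliance marks at Visit 3 and 1 year. If visit attendance was meant by the latter, relabel them.
- **Section 8.3:** state that decolonization compliance is recorded once, at Visit 2 or when the set is returned in hospital, and that only this record is used to define the per-protocol set.
- **Section 11.4:** state that a missing compliance record, or non-compliance, does not remove a randomized episode from the intention-to-treat analysis. Without this, a form missed in hospital would become a dropout in the decolonization arm only, because controls have no form to miss.

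The cost is three table marks and a sentence in each of two sections. The downside is small: some forms missed during the stay will remain missing. An in-hospital record can still follow a very early wound problem, but it comes before most outcome assessments.

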### 1.3 Statistician ("Biostatistician")

Statistical analyses will be performed by the investigators (and eventually the biostatistician [name] [name] of UCAR (Unit for Clinical and Applied Research) using SPSS™ and/or STATA™ software (Version 14). In case of necessity, other biostatisticians will be consulted.

### 1.4 Laboratory

Laboratory analysis will be done by ZLZ Zentrallabor Zürich and IMM, in the immediate vicinity of UKB, as part of the regular analysis of the clinical course.

### 1.5 Monitoring institution

An internal study monitoring board is established to perform ongoing study surveillance and to perform interim analyses if appropriate. UCAR (Unit for Clinical and Applied Research); [name]. med. [name], Balgrist Campus, [name]

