## Study Conduct

The BALGDEC trial is a single-center trial, beginning in February 2023. Only elective surgery patients with a focus on high risk patients for revision and /or SSI according to prior studies will be included, whereas patients with an extraordinary high risk for SSI or impossibility of decolonization will be excluded. At the Balgrist site, this patient population includes: immune-suppressed patients of any type, tumor surgery patients, revision surgery, patients with ASA-Scores 3-4 points or with an age of  $\geq 80$  years; independently of the presence of an orthopedic implant. The operational study team is mainly composed by two infection control nurses, an infectious diseases physician, an orthopedic surgeon with experience in decolonization studies, and the UCAR-team (Unit for Clinical and Applied Research; study nurses).

The infectious control nurses and the infectiologist provide will provide pre-operatively specific instructions regarding the decolonization measure o the patients, and randomize them (1:1) between the presence or absence of the "set" used. The decolonization set will be physically handed over during the inclusion process. The randomization occurs electronically or by prefabricated cards by another study team member not involved in the patient's information process. During decolonization, patients are asked to change the bed linen and underwear every day and not to share towels, clothes and other textiles with their family or pets. They may use their habitual parfums, but must not use other topical antiseptic agents, body lotions or moisturizer during the decolonization period.

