| Publications                         | 
The study team at the Balgrist will present the at least part of the interim results in scientific congresses; and will publish the final results in one or two scientific surgical journals. The Protocol will be published separately, e.g. Journal "Trials".
                                                                                                                                                                                                                                                                                                                                                                                                                                                     |
| Donation                             | 
Schülke & Mayr GmbH will support the study with an unconditional donation of 55,000.- (fifty-five thousand) Swiss Francs (paid in two tranches), which will be used for the salary of the study / infection control nurses, the monitoring and for the Ethical Committee fees. The study team will not make financial profit and cover the minimal operational costs.
 
Schülke & Mayr GmbH will donate all the decolonization kits used for the study, for free (including the corresponding transport costs).
 
Schülke & Mayr GmbH has the rights to consult the data and the draft, but will not be part of the study / academic team that will publish the results of the BALGDEC study.
 |
|                                             |                                                                                                                                                                                                                                                                                                                                                                                                                                                                                                                                                                                                                                                                                                                            |

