### 1.6 Data Safety Monitoring Committee

A data safety committee of two persons with experience in clinical research and biostatistics who are not part of the investigators or future authors of the scientific publication will monitor the safety of data and of the study; during the interim analyses (approximatively after one and two years into the study).

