#### 11.3.1 Interim analysis and early termination

We will perform one interim analysis one year (+/- 2 months) after the inclusion of the first patient. If group comparison between the decolonization and non-decolonization arms are striking and statistically significant in terms of any study objectives, the independent Data Monitoring committee will decide upon the interruption and early termination of the trial. Otherwise, the study continues. Of note, the Data Monitoring committee has the right to call on a premature, additional interim analysis.

If the crude group comparison analysis is not sufficiently meaningful, we will perform a futility analysis to check if the expected statistical power for the final analysis will not be  $< 30\%$  and therefore unacceptable. If it is lower than  $30\%$ , we will consider the trial will not be able to demonstrate the result, and the recruitment will be no more ethical. The most frequent conditional power evaluated under the current trend (i.e. using the information from the collected data) will be assessed. It was demonstrated that futility analyses decrease the statistical power of the final analysis in superiority trials, but in our knowledge, this topic was not explored for non-inferiority trials. To balance (at least partially) this loss of power, we may recruit 100 supplementary patients per arm. E.g. approximately 600 episodes in each randomization arm.

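### The protocol lets the investigators and an internal board run and act on the interim comparison between arms, and does not confine the result to the independent committee

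*Protocol*

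**What the plan says.** Several places in the protocol bear on who produces, sees and uses the interim result.

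- **Section 1.3:** "Statistical analyses will be performed by the investigators"; a UCAR biostatistician is only a possible addition, and outside biostatisticians may be consulted if needed.
- **Section 1.5:** "An internal study monitoring board is established to perform ongoing study surveillance and to perform interim analyses if appropriate". UCAR is named under this heading.
- **Synopsis, Study Conduct:** the operational team includes "the UCAR-team (Unit for Clinical and Applied Research; study nurses").
- **Section 1.6:** "A data safety committee of two persons with experience in clinical research and biostatistics who are not part of the investigators or future authors" is to monitor the study during the interim analyses.
- **Section 2.9:** the Sponsor-Investigators may end the study on early evidence of benefit or harm, with interim analyses given as an example of the source.
- **Section 11.3.1:** "We will perform one interim analysis one year (+/- 2 months) after the inclusion of the first patient". The trigger reads "If group comparison between the decolonization and non-decolonization arms are striking and statistically significant in terms of any study objectives", and the independent committee then decides on termination. Otherwise the study team runs a futility analysis using conditional power under the current trend, and may recruit 100 more patients per arm.
- **Section 10.1.3:** the study team also performs a futility analysis every year.
- **Synopsis, Publications:** the study team "will present the at least part of the interim results in scientific congresses", listed separately from publishing the final results. Section 13 adds preliminary results at meetings.
- **Sections 6.2.2 and 9.1:** there is no blinding of patients. Surgeons assess wounds visually, and the treating physician's opinion prevails in doubtful cases.

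**The concern.** An independent stopping decision protects a trial only if the people running it do not also hold the result. Here the people named as performing the interim comparison belong to, or share a unit with, the team that screens, informs, instructs and randomises patients.

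An open-label trial has few safeguards left once allocation is known to everyone. Withholding the compiled between-arm result is one of them. If the study team knows that decolonization looks better, or looks useless, three things can shift: who is offered the trial, how borderline wounds are called, and whether the optional enlargement is taken up. The enlargement is the most direct route, because section 11.3.1 gives it no rule. Those who may choose it are the same people who compute conditional power from the observed difference.

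**Working it through.** **1. Roles set side by side**

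| Function | Who, according to the protocol |
|---|---|
| Perform statistical analyses | Investigators (1.3) |
| Perform interim analyses | Internal board, UCAR named (1.5); study team (11.3.1) |
| Conditional power, futility | Study team (11.3.1, 10.1.3) |
| Monitor during the interim analyses | Independent committee (1.6) |
| Decide on stopping | Independent committee (11.3.1); Sponsor-Investigators (2.9) |
| Enlarge by 100 per arm | Study team (11.3.1), no rule |
| Present interim results | Study team (synopsis) |

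Conditional power under the current trend cannot be computed without the observed arm difference, so whoever computes it knows that difference. No section names the committee as producer or sole recipient of the comparison, and none withholds it from the investigators.

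**2. The denominator**

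Section 11.2 gives 474 per arm for 10% versus 5%, with 80% power. Section 11.3 gives two-sided 0.05. The usual formula is n = [1.960·√(2·0.075·0.925) + 0.842·√(0.09 + 0.0475)]² / 0.05², which gives 435 per arm. The continuity correction brings this to 474, so the plan's figure reproduces. It is rounded up to 500 per arm, or 1,000 episodes.

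**3. Episodes still to enrol at the interim**

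Remaining = 1,000 − rate × months/12, with even accrual. The rate is 500 per year (1,000 over the 24 months of section 6.1.3) or 600 per year (the minimum availability in the synopsis). The interim is at 12 ± 2 months.

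| Rate per year | Month 10 | Month 12 | Month 14 |
|---|---|---|---|
| 500 | 583 | 500 | 417 |
| 600 | 500 | 400 | 300 |

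**4. Enrolled episodes with follow-up still open**

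- Not yet at day 42: 500 × 42/365 ≈ 58, or 600 × 42/365 ≈ 69.
- The 1-year implant visit has a ± 2 month window, so it opens at 10 months. At a month-12 interim, episodes from the first 2 months could have reached it: 500 × 2/12 ≈ 83, or 600 × 2/12 = 100. At month 14 the figures are 500 × 4/12 ≈ 167, or 600 × 4/12 = 200. At month 10 there are none.
- These counts run from enrolment and ignore the lag to surgery, which would lower them. Only the implant subset matters, and its share is not stated. Even in the most advanced case, at most about 200 of 1,000 episodes could have had the visit.

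**5. How much a shift in outcome calls would matter (illustration only)**

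Assumptions not in the documents: no true effect, 10% event rate, 500 per arm, and a fraction m of decolonization-arm events going unrecorded among the share w of episodes judged after the interim. The recorded rate in that arm is then 0.10·(1 − w·m). The two-sided rejection rate of the 5% test is:

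| w | m = 0 | m = 10% | m = 20% | m = 30% |
|---|---|---|---|---|
| 40% | 5.0% | 5.5% | 7.1% | 10.0% |
| 50% | 5.0% | 5.8% | 8.4% | 13.0% |

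**The case against.** A reader might infer that the second half of the trial will be enrolled and judged with the interim result known. The documents do not support that, for five reasons.

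- **Surgeons.** Section 9.1 gives wound judgement to orthopaedic surgeons and the treating physician. No passage says that treating surgeons in general receive interim data.
- **UCAR.** The board's membership is not visible. That the same persons sit on it and work as study nurses is inferred from a shared unit name.
- **Congresses.** The synopsis gives no date and does not say that results will be shown by arm. Pooled or questionnaire data would satisfy the sentence.
- **Follow-up.** It would be too strong to say that essentially all 1-year implant outcomes are judged afterwards. The visit window lets some early cases complete, and infections and revisions before the interim are already recorded.
- **Added bias.** Everyone already knows individual allocations. The section 3.2.1 definition of infection needs two positive intraoperative samples, and a wound problem there requires surgical revision, which limits discretion. The under-recording rates in the illustration are invented.

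These points reduce the claim to a risk. They do not remove it. The investigators and the internal board know the comparison because they are the ones assigned to perform it. Knowing one patient's arm is different from holding a tested between-arm result. The decision to revise a wound, which comes before any intraoperative sample, remains a clinical judgement.

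It can also be said that access rules belong in a committee charter or SAP. That would answer a silent protocol. This one states an arrangement, and the arrangement conflicts with the independence that section 1.6 sets up.

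**Conclusion.** The point holds as a risk created by the stated allocation of roles. Sections 1.3, 1.5, 2.9 and 11.3.1 have the investigators and an internal board perform, or act on, the interim arm comparison and conditional power, while the section 1.6 committee decides on stopping without being the only party to see them.

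With even accrual, about 400 to 500 of 1,000 episodes remain to enrol at month 12, and 300 to 583 across the full timing window and 500 to 600 episodes per year. Most 1-year implant follow-ups would also be open. The size of any resulting bias cannot be derived from the documents. The rejection rates above show only that modest differential recording would matter. The matter should be corrected before the interim. It does not by itself invalidate the design, and it does not change the sample size.

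**What to change.** Reconcile sections 1.3, 1.5, 1.6, 2.9 and 11.3.1, and the sentence on annual futility analysis in 10.1.3, so that they say the same thing:

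- The by-arm interim comparison and conditional power are run and seen only by the section 1.6 committee. Either its member with biostatistics experience does the work, or a biostatistician outside the study team who reports only to the committee, which section 1.3 already allows.
- The internal board keeps ongoing surveillance but does not perform by-arm interim analyses.
- The study team receives only a recommendation: continue, stop, or continue with the enlargement. The enlargement follows a rule written down before the interim.
- Section 2.9 refers to the committee's recommendation wherever stopping rests on interim evidence.
- In the synopsis and section 13, anything presented before the last outcome is pooled across arms.
- The interim reports promised to the ethics committee in section 2.5 are pooled, or come directly from the section 1.6 committee where arms are shown.

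The cost is a wording amendment, the loss of a by-arm congress abstract before the trial ends, and a little analysis work for the committee. The budget has no line for a statistician, so if an outside one is used, that time has to be found.
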